#### Baseline characteristics

• Risk factors and comorbidities:

– Age;

– Gender;

– Hypertension: Systolic blood pressure ≥140 mmHg and/or diastolic blood pressure ≥ 90 mmHg, or if the patient is on antihypertensieve therapy for the indication of hypertension;

– Hyperlipidemia: LDL-cholesterol >4.4 mmol/L (>170 mg/dL) or triglycerides >2.0 mmol/L (>177 mg/dL), or if the patient is taking lipid-lowering medication for the indication of hyperlipidemia;

– Diabetes mellitus: HbA1c >7% or if the patient consumes oral hypoglycemic agents or uses insulin;

– Smoking: Current smoking status (active/previous/never), number of pack years, number of years since last smoked;

– Ischemic heart disease: History of myocardial infarction, angina pectoris, previous percutaneous or surgical coronary revascularization, positive exercise test, anti-anginal therapy;

– Congestive heart failure: Ejection fraction <40%;

Renal insufficiency: e-GFR <60 mL/min/1.73 m^2;^

– Cerebrovascular disease: Known carotid artery disease and history of minor or major stroke or transient ischemic attack (TIA).

• Medication, pre-, peri- and post-procedural, (including dose, frequency and duration of use):

– Anticoagulants (Acenocoumarol, Fenprocoumon, unfractioned or low molecular weight heparins, and so on);

– Antithrombotic agents (Acetyl salicylic acid, Clopidrogel, Dipyridamol, and so on);

– Statins or other lipid-lowering agents;

– Beta-blockers;

– Angiotensin converting enzyme inhibitors;

– Angiotensin-II receptor antagonists;

– Insulin and oral hypoglycaemic agents;

– Medications for the treatment of IC (Pentoxifylline, Buflomedil).

• Baseline anatomic characteristics of the target lesion in the common iliac artery, as determined by DSA and pre-operative CT-angiography or MR-angiography:

– Arterial inflow: Impaired inflow is defined as presence of hemodynamically significant obstruction in the aorta;

– Arterial outflow: Impaired outflow is defined as presence of hemodynamically significant obstruction in the external iliac artery, common femoral artery or both superficial and deep femoral arteries. Isolated hemodynamically significant obstruction in either the superficial or deep femoral artery will not be considered impaired outflow;

– Reference vessel diameter, obtained from averaging 5mm segments proximal and distal to the lesion;

– Involvement of origin/ostium;

– Lesion length, documented in centimeters and classified as follows:

– Cerebrovascular disease: Known carotid artery disease and history of minor or major stroke or transient ischemic attack (TIA).

• Medication, pre-, peri- and post-procedural, (including dose, frequency and duration of use):

– Anticoagulants (Acenocoumarol, Fenprocoumon, unfractioned or low molecular weight heparins, and so on);

– Antithrombotic agents (Acetyl salicylic acid, Clopidrogel, Dipyridamol, and so on);

– Statins or other lipid-lowering agents;

– Beta-blockers;

– Angiotensin converting enzyme inhibitors;

– Angiotensin-II receptor antagonists;

– Insulin and oral hypoglycaemic agents;

– Medications for the treatment of IC (Pentoxifylline, Buflomedil).

• Baseline anatomic characteristics of the target lesion in the common iliac artery, as determined by DSA and pre-operative CT-angiography or MR-angiography:

– Arterial inflow: Impaired inflow is defined as presence of hemodynamically significant obstruction in the aorta;

– Arterial outflow: Impaired outflow is defined as presence of hemodynamically significant obstruction in the external iliac artery, common femoral artery or both superficial and deep femoral arteries. Isolated hemodynamically significant obstruction in either the superficial or deep femoral artery will not be considered impaired outflow;

Reference vessel diameter, obtained from averaging 5mm segments proximal and distal to the lesion;

Involvement of origin/ostium;

Lesion length, documented in centimeters and classified as follows:

▪ Focal: ≤1 cm;

▪ Short: >1 and <3 cm;

▪ Intermediate: ≥ 3 and < 5 cm;

▪ Long: ≥ 5 cm;

▪ In case of vessel occlusion with a stenosed segment, both the length of the stenosed segment and the length of the occluded segment should be reported.

– Occlusion or stenosis

– In case of stenosis

▪ Minimal luminal diameter;

▪ Percent diameter stenosis;

▪ Systolic pressure gradient, measured as described previously.

– Calcification: Semi-quantitative distinction between no, moderate, and heavy calcification at the site of the lesion.

– TASC-classification.

• Baseline anatomic characteristics of other hemodynamically significant lesions at the aortoiliac and femoropopliteal level:

– Arterial segment(s):

▪ Infra-renal abdominal aorta;

▪ Internal iliac artery;

▪ External iliac artery;

▪ Common femoral artery;

▪ Deep femoral artery;

▪ Superficial femoral artery;

▪ Popliteal artery.

– Lesion length, documented in centimeters and classified as follows:

▪ Focal: ≤1 cm;

▪ Short: >1 and <5 cm;

▪ Intermediate: ≥ 5 and < 15 cm;

▪ Long: ≥ 15 cm;

▪ In case of vessel occlusion with a stenosed segment, both the length of the stenosed segment and the length of the occluded segment should be reported.

– Occlusion or stenosis

• Crural outflow: Each of the crural arteries with patency directly to the foot will score 1 point. A patent dorsal and plantar pedal arch will each score 1 point. This will lead to a score of 0 to 5, indicating crural outflow. As it is not standard procedure to make a DSA of the crural arteries during iliac interventions, pre-operative CT-A or MR-A will be used to score this.

• Presence of multilevel disease: Defined as presence of significant obstructive lesions at more than one level in the same limb (aortoiliac, femoropopliteal and crural). When patients are included with both limbs, one limb can have multilevel disease, while the other limb does not.

• Disease-related health status and quality of life: As defined by the Walking Impairment Questionnaire (WIQ) and RAND-36 questionnaire.

• Rutherford stage.

• Functional status:

– In patients with IC: Claudication onset time (COT) and absolute claudication time (ACT) on a standardized treadmill test (3.2 km/h at a 12% grade for a maximum of 5 minutes).

• Hemodynamic status:

– In patients with IC: ABI at rest and after standardized treadmill test;

– In patients with CLI: Systolic ankle pressure and ABI.

• Degree of stenosis and peak systolic velocity ratio on DUS.

#### Procedure-related parameters

• Grams of intravenous iodine used for contrast. The amount of millilitres used will be scored during the procedure, and post-hoc the amount of iodine will be calculated. In our centre, we use Visipaque®, which contains 320mg of Iodine per ml

• Radiation time and dosage, as is measured by the fluoroscopy device

• Amount and type of materials used (guidewires, sheaths, balloons, catheters)

• Type, diameter, number and length of stents used

• Lesion characteristics after treatment:

– Arterial inflow: Impaired inflow is defined as presence of hemodynamically significant obstruction in the aorta;

– Arterial outflow: Impaired outflow is defined as presence of hemodynamically significant obstruction in the external iliac artery, common femoral artery or both superficial and deep femoral arteries. Isolated hemodynamically significant obstruction in either the superficial or deep femoral artery will not be considered impaired outflow;

– Minimal luminal diameter (MLD);

– Percent diameter stenosis;

– Systolic pressure gradient.

• Peri-procedural complications.

• Technical success

• Device success

#### Parameters scored during regular follow-up

• Disease-related health status and quality of life: As defined by the Walking Impairment Questionnaire (WIQ) and RAND-36 questionnaire.

• Rutherford stage.

• Functional status:

– In patients with IC: Claudication onset time (COT) and absolute claudication time (ACT) on a standardized treadmill test (3.2 km/h at a 12% grade for a maximum of 5 minutes).

• Hemodynamic status:

– In patients with IC: ABI at rest and after standardized treadmill test;

– In patients with CLI: Systolic ankle pressure and ABI.

• Degree of stenosis and peak systolic velocity ratio on DUS.

• Occurrence of amputation.

• Mortality.

#### Parameters scored in case of restenosis or reocclusion

• Anatomic characteristics of the restenosis or occlusion in the stent in the common iliac artery:

– Arterial inflow: Impaired inflow is defined as presence of hemodynamically significant obstruction in the aorta.

– Arterial outflow: Impaired outflow is defined as presence of hemodynamically significant obstruction in the external iliac artery, common femoral artery or both superficial and deep femoral arteries. Isolated hemodynamically significant obstruction in either the superficial or deep femoral artery will not be considered impaired outflow.

– Relation of stenosis or occlusion to the stent:

▪ Proximal edge, defined as 1 cm proximal and distal to the proximal edge of the stent;

▪ In-stent, defined as 1 cm distal from the proximal to 1 cm proximal from the distal end;

▪ Distal edge, defined as 1 cm proximal and distal to the distal edge of the stent.

– Lesion length, documented in centimeters and classified as follows:

▪ Focal: ≤1 cm;

▪ Short: >1 and <3 cm;

▪ Intermediate: ≥ 3 and < 5 cm;

▪ Long: ≥ 5 cm;

▪ In case of vessel occlusion with a stenosed segment, both the length of the stenosed segment and the length of the occluded segment should be reported.

– Occlusion or stenosis;

– In case of stenosis:

▪ Minimal luminal diameter;

▪ Percent diameter stenosis;

▪ Systolic pressure gradient.

• Procedural success rate of re-intervention.

### Randomization, blinding and treatment allocation

All symptomatic patients in whom a hemodynamically significant lesion of the CIA is suspected will be included. This is assessed using DUS and either CT-angiography or MR-angiography. A hemodynamically significant lesion is suspected if DUS shows a peak systolic velocity ratio of ≥2.4 and/or CT-angiography or MR-angiography shows a diameter reduction of ≥50%. Any suspected significant lesion is initially included, and informed consent obtained, even if pre-operative imaging shows a stenosis with a length of less than 3 cm. After the pre-intervention DSA and intra-arterial systolic blood pressure gradient measurement have been performed, the treating physician will make the final decision if the patient meets the inclusion criteria. If there is a stenosis with a length of more than 3 cm, or an occlusion, the patient will be randomized. All patients with stenoses with a length of less than 3 cm will be excluded, but they will be registered, and informed consent will have been obtained to store their data (Figure 2). Randomization will be performed using an online registration and randomization program (Trans European Network for Clinical Trial Services (TENALEA), http://tenalea.net). Unstratified randomization will be used, with a minimization algorithm based on occlusion vs stenosis, and endovascular vs hybrid procedures. If a patient has bilateral iliac lesions that are eligible, the symptomatic limb will be included. In case both limbs are symptomatic, the leg with the lowest ABI will be included. Both legs will receive the same treatment. The patient will be allocated to either the Advanta V12 PTFE-covered stent, or to an uncovered balloon-expandable stent. Patients will be blinded for the treatment they receive. When patients are under local or regional anesthesia, a sterile operating theatre napkin will be placed in such a manner that the patient cannot see the procedure and the stent in particular. The physician will make sure not to mention the type of stent prior, during or after the procedure. The physician performing the procedure will not be blinded, as this is not possible practically. The type of stent used will not be documented in the patient’s medical record. Post-operative ABI’s, DUS and scoring of Rutherford classification will be performed by vascular technicians who are blinded for the type of stent used. Therefore, this is a double-blind study.

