#### Sample size calculation

Based on the available literature [53,54], we expect a 2-year absence of binary restenosis rate of 90% in the PTFE-covered stent group, and a 2-year absence of binary restenosis rate of 72% in the uncovered stent group. Based on the log rank test for equality of survival curves, with an alpha error level of 0.05 and a beta error level of 0.2, 79 patients per group will be necessary. We anticipate a loss to follow-up of less than 10%, so we will include 87 patients per group, for a total of 174 patients. This calculation was performed using nQuery Advisor (Statistical Solutions Ltd., Farmer’s Cross, Ireland). The combined participating centers perform over 200 endovascular procedures for advanced iliac PAOD annually. With an estimated participation rate of 75%, estimated inclusion time is 2 years.

No sample size calculation was performed for the subgroups as there is no data available on freedom of binary restenosis rates for these groups, and therefore no well-founded calculation can be made.

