#### Treatment of the common iliac artery

A 6F or 7F sheath (depending on the type and diameter of the stent) is introduced into the ipsilateral common femoral artery. If necessary an adjunctive contralateral approach may be used at the discretion of the physician, either to make angiographic images, or to facilitate passage of the diseased segment. All patients receive 5,000 units of unfractionated heparin. A diagnostic catheter is introduced into the aorta over a 0.035-inch guidewire. Digital Subtraction Angiography (DSA) is performed and saved according to protocol. In stenoses, the pressure gradient is measured using a 70cm straight catheter (4F) without side holes, which is withdrawn through the stenosis. A translesional systolic blood pressure gradient of >10mmHg is considered significant. The pressure gradient, as well as absolute pressures, are documented. The length of the diseased segment is measured per-operatively on the DSA-images, and based on the pressure gradient and length measurement the final decision is made whether or not to include and randomize the subject. Any occlusion is included, as well as any stenosis longer than 3 cm. Serial lesions less than 2 cm apart will be regarded as one long stenosis and will be randomized.

Based on randomisation, an Advanta V12 stent or a balloon-expandable uncovered stent is placed. A stenosis should be fully covered by the stent, including 5mm proximal and distal to the stenosis, based on the inflated length of the stent. In case of proximal lesions, in which the stent would extend into the aorta, and in distal lesions, in which the stent would cover the internal iliac artery (IIA), this 5mm margin is not mandatory. In case of a stenosis including the distal aorta or iliac bifurcation, ‘kissing stents’ will be placed, which will extend into the aorta. In case of a stenosis extending into the EIA, the lesion in the CIA will be treated with a balloon-expandable stent. The stenotic segment extending into the EIA will be treated with PTA alone, PTA and a self-expanding stent or remote endarterectomy. We try to avoid covering the IIA with a stent.

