### Follow-up of subjects withdrawn from treatment

Patients that for whatever reason receive a different treatment than randomized, or received no treatment will be followed-up and included in the trial, based on intention-to-treat. Patients that are withdrawn from follow-up will be considered lost to follow-up.

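### The protocol does not require an occlusion to be crossed before randomisation, and never-opened limbs have neither a scoring rule nor a sample-size allowance

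*Protocol article*

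**What the plan says.** All references are to the protocol article.

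- **Trigger for randomisation.** Under Randomization, blinding and treatment allocation, after the angiogram and pressure measurement: "If there is a stenosis with a length of more than 3 cm, or an occlusion, the patient will be randomized". Treatment of the common iliac artery adds: "Any occlusion is included, as well as any stenosis longer than 3 cm". Neither section, nor the inclusion criteria, makes crossing a condition.
- **Order of steps.** Treatment of the common iliac artery describes an ipsilateral femoral sheath, a diagnostic catheter taken to the aorta over a guidewire, the angiogram, the gradient measurement in stenoses, and then the decision to randomise. A contralateral approach is optional, for imaging or to help cross the lesion. Stent placement follows, and then the text on recanalising an occlusion.
- **Untreated patients.** Follow-up of subjects withdrawn from treatment says that randomised patients who "received no treatment will be followed-up and included in the trial, based on intention-to-treat".
- **Endpoint.** The primary endpoint is absence of a haemodynamically significant obstruction in the target lesion following endovascular treatment. No rule covers a lesion that was never opened.
- **Sample size.** The planning rates at 2 years are 90% free of restenosis with the covered stent against 72% with uncovered stents. For the log-rank test, "with an alpha error level of 0.05 and a beta error level of 0.2, 79 patients per group will be necessary". This is raised to 87 per group for loss to follow-up, and no other allowance is made.

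**The concern.** The two lesion types are treated differently at the point of randomisation. In a stenosis the gradient catheter is withdrawn through the lesion first, so crossing is already proven when the patient is allocated. An occlusion has no such step, and the angiographic finding alone is enough.

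If an occlusion is randomised and then cannot be recanalised, neither stent is placed. The outcome says nothing about stent type, yet the patient stays in the comparison. If such limbs are scored as obstructed, the same number of extra failures enters each arm, the difference between the arms shrinks and its variance rises. If they are not scored, evaluable patients are lost. The protocol does not choose between these, so both the power and the meaning of the primary estimate depend on an unstated rule and an unstated rate.

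**Working it through.** **Inputs.** From Sample size calculation: 2-year rates of 90% and 72%, log-rank test, alpha 0.05, power 80%, 79 per group, 87 after loss to follow-up. Assumed: f, the share of all randomised patients with a never-opened occlusion, equal in both arms, shown from 0 to 10%. The protocol gives neither the share of occlusions nor a crossing-failure rate.

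**1. Reproduce the planned number (Freedman, two-sided).**

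- HR = ln 0.90 / ln 0.72 = 0.321
- Events = (1.960 + 0.842)² × [(1 + 0.321)/(1 − 0.321)]² = 29.7, rounded up to 30
- Per arm = 30 / (0.10 + 0.28) = 78.9, so 79, which matches the plan
- 79 × 1.10 = 86.9, so 87, which also matches

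**2. Add never-opened limbs as failures in both arms.** The rates become 0.90(1 − f) and 0.72(1 − f), and the 18-point difference becomes 18(1 − f). With n per arm,

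power = Φ( √(n × (2 − p₁ − p₂)) × (1 − HR)/(1 + HR) − 1.96 ), where HR = ln p₁ / ln p₂.

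For f = 5% and n = 79: rates 0.855 and 0.684; HR = 0.412; events = 79 × 0.461 = 36.4; power = Φ(6.035 × 0.416 − 1.96) = Φ(0.55) = 70.9%.

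| f | Power, 79 per arm | Power, 87 per arm (no loss) | Evaluable n per arm for 80% |
|---|---|---|---|
| 0 | 80.5% | 84.1% | 79 |
| 1% | 78.5% | 82.3% | 82 |
| 2% | 76.6% | 80.5% | 86 |
| 5% | 70.9% | 75.0% | 99 |
| 10% | 62.0% | 66.2% | 121 |

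The slope is (80.5 − 70.9)/5 = 1.9 points of power per 1%.

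**3. Cross-checks at 79 per arm.** For f = 0, 2, 5 and 10%, a two-proportion calculation gives 82.9%, 78.8%, 72.7% and 63.2%. A log-rank simulation (3,000 runs, never-opened limbs failing at time 0, other failures detected at 6, 12 or 24 months) gives 82.4%, 79.6%, 71.2% and 58.0%. The pattern is the same.

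**4. Alternative scoring.** If never-opened limbs contribute no endpoint data, the evaluable number is 79(1 − f) at the planned rates. Power is then 79.7% at f = 2%, 78.4% at 5% and 76.2% at 10%.

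**5. What f means.** It is the share of occlusions multiplied by the share of those not crossed. If half of the patients had occlusions (an assumption), f = 2% would be 0.02/0.5 = 1 in 25 occlusions and f = 5% would be 1 in 10.

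**The case against.** The strongest reply is that the protocol's own sequence already puts crossing first. From an ipsilateral groin sheath, a catheter reaches the aorta only through the common iliac artery, and this step comes before the angiogram and the decision to randomise. On that reading an uncrossable occlusion is never randomised, and the rule that patients withdrawn before randomisation are replaced and documented already covers it. This stands in part. A reader might infer that occlusions are randomised before the guidewire has crossed, but no section says so. What survives is that crossing is never made a condition, that contralateral imaging is allowed, and that the section is not a strict chronology: it opens by sizing the sheath to the stent type, which is allocated later. The inclusion flowchart (Figure 2) was not legible for this review and may settle the order.

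Second, a reader might infer that never-opened limbs are intention-to-treat failures. The protocol keeps them in the analysis but does not say how they are scored. Failure is the natural reading if the artery stays obstructed at duplex, but the endpoint's restriction to status following treatment permits another.

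Third, it is tempting to say that 80% power holds only if practically every occlusion is crossed. That is too strong, because 87 per arm still gives 80.5% at f = 2% if nobody is lost.

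Fourth, the Background's figure of about 80% technical success cannot supply f. It comes from an earlier trial that excluded advanced disease, and technical success is not a crossing rate. Nor can it be checked whether the 90% and 72% taken from cited studies already include technical failures.

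Finally, minimisation on occlusion versus stenosis tends to balance such limbs between arms. Operators are unblinded, so persistence could in principle differ by arm if crossing followed allocation, but nothing in the protocol shows that it would.

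**Conclusion.** The point holds as an unfixed design step. The protocol permits, without saying that it happens, randomisation of occlusions that are never opened. It keeps such patients in the analysis, does not say how they are scored, and makes no allowance for them in the sample size.

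The consequence is dilution of the stent comparison, not bias. Its size rests on three assumptions: the rate f, equal rates in both arms, and planning rates that do not already include technical failures. If the limbs count as failures, the loss is about 2 points of power per 1% at 79 per arm: minor at f = 1% and material at 5% (70.9%). If they contribute no endpoint data, it is about 2 points at f = 5% and 4 points at 10%. The change is worth making because it costs very little and removes dependence on a rate that the protocol does not state.

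**What to change.** 1. In Treatment of the common iliac artery and in Randomization, blinding and treatment allocation, state that the online randomisation of an occlusion is done only after successful guidewire crossing and before the stent type is known.
2. Register uncrossed occlusions without randomising them, as the protocol already does for stenoses shorter than 3 cm.
3. Keep intention-to-treat for everyone randomised.
4. Under Primary endpoint, state how a randomised but never-opened limb is scored. Some may still occur after crossing.

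**Cost.** This is a change of protocol wording, and the randomisation call moves by minutes within the same procedure. Lesion type and procedure type remain available for the minimisation. The downside is that results apply to crossed lesions, but that is the population in which a stent is chosen.

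**Alternative.** If the sponsor prefers to randomise on the angiogram alone, state the assumed f and the scoring rule, and resize. With never-opened limbs counted as failures at f = 5%, this means 99 evaluable per arm, or 99 × 1.10 = 108.9, so 109 per arm with the protocol's own inflation.

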### Distal outflow after endovascular repair

Several studies have shown that decreased outflow leads to lower patency rates and that, when treating the iliac artery endovascularly, sufficient outflow from the common femoral artery is mandatory [37,41].

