### Study Design

A prospective, randomized, controlled, double-blind, multi-center trial with a follow-up period of 2 years.

Centers currently participating are:

• Maasstad Hospital, Rotterdam, The Netherlands

• Sint Antonius Hospital, Nieuwegein, The Netherlands

More centers may be added during the course of the trial.

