#### Name and description of control group products

In the control group, several uncovered balloon-expandable stents have been selected to choose from at the physician’s discretion. These stents are currently used in the participating centers.

Omnilink Elite stent (Abbott Laboratories, North Chicago, IL, USA). The Omnilink Elite is a balloon-expandable CoCr (cobalt chromium alloy) stent. It is available in diameters of 4 to 10 mm. Available lengths are 12, 16, 19, 29, 39 and 59 mm. All Omnilink Elite stents are 0.035-inch guidewire compatible and are pre-mounted on a 6F dual layer compliant balloon catheter. Available catheter lengths are 80 and 135 cm. It is registered for use in the iliac artery in Europe.

Dynamic stent (Biotronik, Berlin, Germany). The Dynamic stent is a balloon-expandable stainless steel stent, with the stent struts coated with an amorphous silicon carbide coating. It is available in diameters of 5 to 10 mm. Available lengths are 15, 25, 38 and 56 mm. All Dynamic stents are 0.035-inch guidewire compatible and are pre-mounted on a 6 or 7F compliant balloon catheter. Available catheter lengths are 80 and 130 cm. It is registered for use in the iliac artery in Europe.

Express LD Iliac stent (Boston Scientific, Natick, MA, USA). The Express LD Iliac is a balloon-expandable stainless steel stent. It is available in diameters of 6 to 10 mm. Available lengths are 20, 30, 40 and 60 mm. All Express LD Iliac stents are 0.035-inch guidewire compatible and are pre-mounted on a 6 or 7F compliant balloon catheter. Available catheter lengths are 75 and 135 cm. It is registered for use in the iliac artery in Europe.

Palmaz Genesis stent (Cordis Corporation, Bridgewater, NJ, USA). The Palmaz Genesis is a balloon-expandable stainless steel stent. It is available in diameters of 4 to 10 mm. Available lengths are 12, 15, 18, 19, 24, 25, 29, 39 and 59 and 79 mm. In the participating centers, we only use 24, 39, 59 and 79 in the common iliac artery. All Palmaz Genesis Iliac stents are 0.035-inch guidewire compatible and are pre-mounted on a 6 or 7F compliant balloon catheter. Available catheter lengths are 80 and 135 cm. It is registered for use in the iliac artery in Europe.

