#### Pre-operative

Pre-operative, DUS will be performed to document the occlusion or degree of the stenosis in the iliac and common femoral artery. This is mandatory, as this is the modality that will be used during follow-up. Additionally, either CT-angiography (CT-A) or MR-angiography (MR-A) of the entire lower extremity must be performed at the physician’s discretion. An ABI will be measured, including a treadmill test in claudicants. These are all part of our regular pre-operative work-up. In most cases, one or more of these investigations will have been performed prior to inclusion. When this has been no longer than 3 months prior to inclusion, the investigation will not have to be repeated for study purposes. All other relevant study parameters will be documented and patients will be asked to fill in the RAND-36 and WIQ.

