### Statistical analysis

Statistical analysis will be performed for the complete study population, as well as subgroup analysis for patients with IC vs CLI, occlusions vs stenoses, and endovascular vs hybrid procedures.

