
## Abbreviations

AE: Adverse Event; AIOD: Aorto-iliac occlusive disease; CCMO: Central Committee on Research Involving Human Subjects; in Dutch: Centrale Commissie Mensgebonden Onderzoek; CIA: Common Iliac Artery; CLI: Critical limb ischemia (Rutherford category 4 5 or 6); DUS: Duplex ultrasonography; EU: European Union; GCP: Good Clinical Practice; IC: Informed Consent; METC: Medical research ethics committee (MREC) in Dutch: medisch ethische toetsing commissie; PAOD: Peripheral arterial occlusive disease; PTFE: Polytetrafluoroethylene; (S)AE: (Serious) Adverse Event; TER: Target-extremity revascularization; TLR: Target-lesion revascularization; WMO: Medical Research Involving Human Subjects Act (in Dutch: Wet Medisch-wetenschappelijk Onderzoek met Mensen; Wbp: Personal Data Protection Act (in Dutch: Wet Bescherming Persoonsgevens).

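### Minimisation covers two of the three planned subgroup factors and omits IC vs CLI, which is known before allocation; the cost falls on the CLI subgroup and the baseline table, not on the validity of the primary test

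*Protocol article*

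**What the plan says.** - **Allocation** (Randomization, blinding and treatment allocation): "Unstratified randomization will be used, with a minimization algorithm based on occlusion vs stenosis, and endovascular vs hybrid procedures". The list is complete as written, and no reason is given for its limits.
- **Subgroups** (Statistical analysis): "subgroup analysis for patients with IC vs CLI, occlusions vs stenoses, and endovascular vs hybrid procedures". The second and third pairs are minimisation factors; the first is not.
- **When IC/CLI is known.** Rutherford stage is listed under Baseline characteristics. The Background assigns categories 1 to 3 to IC, and the Abbreviations give "CLI: Critical limb ischemia (Rutherford category 4 5 or 6". The Pre-operative section says "An ABI will be measured, including a treadmill test in claudicants", so claudicants are identified before the procedure. Allocation comes later: during the procedure, "based on the pressure gradient and length measurement the final decision is made whether or not to include and randomize the subject" (Treatment of the common iliac artery).
- **Link to outcome.** The Background associates CLI with multilevel disease that reaches below the groin. The section on distal outflow reports that "decreased outflow leads to lower patency rates". The section on endovascular treatment gives open-repair patency of 85 to 92% in IC and 78 to 83% in CLI.
- **Analysis** (Actuarial analysis): the primary endpoint is compared by log-rank test, with no covariate adjustment named.
- **Sizing** (Sample size calculation): 79, raised to 87, per group. The subgroups are expressly not sized.

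**The concern.** Two of the three subgroup factors were thought worth balancing and the third was left to chance, although it can be entered in the randomisation system at no cost and the article itself treats it as related to patency. Allocation factors cannot be repaired afterwards; analysis can only adjust for what happened. Two things are at stake. The stent comparison within CLI may rest on unequal arms in a group nobody has sized. And the baseline table may show more CLI in one arm, while the only primary test named is unadjusted, so readers would be left to judge how much the difference matters.

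**Working it through.** **1. The plan's own figure.** Inputs from Sample size calculation: 90% vs 72% free of restenosis at 2 years, alpha 0.05 (taken as two-sided), power 80%.

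- Hazard ratio = ln(0.90)/ln(0.72) = 0.321.
- Freedman events = 30. Mean event rate = (0.10 + 0.28)/2 = 0.19. 30/0.19 = 157.9, or 79 per group, as stated.
- 79 × 1.10 = 87 per group, 174 in total, as stated.

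The sample size reproduces and does not depend on this point.

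**2. Chance imbalance in CLI.** The article gives no CLI share, so it is assumed. With K CLI patients among 174 and 87 per arm, the number in one arm is hypergeometric. The SD of the difference in CLI share is 2 × SD/87. Subgroup efficiency relative to an even split is 4ab/K² for a split a v b.

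| Assumed CLI share | K | SD of difference in share | Chance of 10 points or more | 95% range of split | Efficiency at that extreme |
|---|---|---|---|---|---|
| 10% | 17 | 4.5 points | 4% | 5 v 12 | 0.83 |
| 15% | 26 | 5.4 points | 5% | 8 v 18 | 0.85 |
| 25% | 44 | 6.6 points | 12% | 16 v 28 | 0.93 |
| 35% | 61 | 7.3 points | 20% | 24 v 37 | 0.95 |

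At 25%: 4 × 16 × 28/44² = 1792/1936 = 0.93. The model treats CLI as unrelated to the two factors already minimised, so these figures are probably upper values.

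**3. Shift in the primary difference.** Shift = imbalance × gap in freedom from restenosis between IC and CLI. The only IC/CLI figures in the article (open repair) give a gap of 2 points (85 − 83) to 14 points (92 − 78), and 8 points at the midpoints (88.5 − 80.5).

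- At 25% CLI and an 8-point gap, the SD of the shift is 0.066 × 8 = 0.5 points.
- At the 16 v 28 extreme the imbalance is 12/87 = 13.8 points, so the shift is 0.138 × 8 = 1.1 points (0.3 to 1.9 over gaps of 2 to 14).
- For comparison, the planned difference is 18 points, and its SE with 79 per arm is √[(0.72 × 0.28 + 0.90 × 0.10)/79] = 6.1 points. As a share of variance, (0.5/6.1)² is under 1%.

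**4. Effect on the primary test.** Log-rank simulation: 174 patients, 2 years, 10% loss, CLI share 20% or 40%, CLI hazard ratio 1 to 3 (the open-repair ranges imply about 1.15 to 2.98), 4,000 runs per setting.

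- Type I error with IC/CLI left to chance: 0.048 to 0.059 (simulation SE about 0.003).
- Power, unadjusted test: 0.86 left to chance; 0.85 to 0.87 balanced.
- Power, test stratified by IC/CLI, at a CLI hazard ratio of 3: 0.87 to 0.89.

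**The case against.** A subgroup factor need not be an allocation factor, and choosing two factors for 174 patients is a legitimate choice. That stands: nothing here is contradictory or invalid.

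The protocol also acts on the route by which CLI would affect patency. It makes adequate femoral outflow a treatment aim, requires endarterectomy for significant common femoral disease, and minimises on endovascular vs hybrid procedures. Part of the CLI effect is therefore probably treated or balanced already, though the article does not show how much. This limits the size of the point but does not replace balance on a factor that is analysed as its own subgroup. The open-repair figures are also not iliac stent figures; they show direction more than size.

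Two stronger readings are tempting.

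- *That a CLI imbalance would bias the primary comparison.* Chance imbalance under random allocation is already reflected in the standard error and p-value, and the simulation shows no inflation of type I error. A shift near 3 points arises only by stacking assumptions: a large CLI share, a 20-point gap and a two-SD imbalance (0.146 × 20 = 2.9).
- *That leaving out centre confounds the stent comparison with the operator or the control product.* The article does say "More centers may be added during the course of the trial", and for controls "several uncovered balloon-expandable stents have been selected to choose from". But only control patients receive those products, so balancing arms within a centre would not alter which one is picked or separate product from centre. In a 20-patient centre the 95% range of 6 to 14 in one arm still leaves both arms represented. Minimising within centre would also make the next allocation easier to guess for an unblinded physician who decides eligibility just before randomisation. Leaving centre out is therefore defensible.

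**Conclusion.** The point holds as a minor, inexpensive improvement. The allocation scheme omits the third planned subgroup factor, which is available at allocation and which the article links to patency. It does not threaten the validity of the primary analysis, and its effect on power is within simulation noise unless CLI is strongly prognostic, where most of the small gain comes from adjustment. The remaining cost is uneven arms in the CLI subgroup (efficiency at the 95% extreme of about 0.83 at a 10% CLI share, 0.93 at 25%) and a chance imbalance that would be visible at baseline. These sizes rest on an assumed CLI share, an assumed IC/CLI gap, and CLI being independent of the two minimised factors.

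**What to change.** Add IC vs CLI (Rutherford 1 to 3 vs 4 to 6) to the TENALEA minimisation and confirm that the algorithm keeps a random element. Trial status gives inclusion as still to start, so on the text as written this can be done before the first allocation. Keep the log-rank test as primary and support it with a stratified log-rank test or a Cox model adjusted for the minimisation factors. If IC/CLI was left out on purpose, one sentence giving the reason would settle the mismatch. Treat centre as optional, weighing balance against predictability.

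Cost: one more minimisation factor, a system setting, a sentence in the protocol and a little more analysis. The sample size stays at 174.
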